### Statistical analysis

Statistical analysis will be carried out by a certified health professional using STATA software (College Station, TX, USA). Data will be descriptively analyzed and presented as percentage or mean ± standard deviation for all clinical variables, median ± interquartile (IQ) range for variables without a normal distribution, and percentage for categorical and binary variables. The Kolmogorov–Smirnov test will test the distribution and normality of variables. To compare groups at T0, the Student *t*-test, the Mann–Whitney-Wilcoxon test for continuous variables, and the chi-squared test for categorical variables will be used.

Two-way analysis of variance (ANOVA) will analyze the effects of the intervention for repeated measures (time and group). A post hoc analysis will be conducted when the ANOVA *F* ratio is significant for the Student *t*-test among times and groups, and Bonferroni’s correction will be applied. Statistical significance is defined as *P* = 0.05.

Data will be primarily analyzed according to the intention-to-treat principle. An on-treatment analysis will be subsequently performed to assess whether protocol deviations have caused bias. Participants with documented deviation from the study protocol (i.e., patients in the intervention group who received only some of the intervention or participants in both groups with incomplete follow-up data) will be excluded.

No interim analysis is planned as no harm to patients is expected from this trial. There is no reason to stop prematurely other than the end of the financing.

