**Methods and analysis:**

During scheduled outpatient cardiology evaluations, eligible patients are recruited and randomly assigned to either an intervention or control group in a 1:1 ratio. The intervention group receives support from a nursing case manager through a structured home-based teleassistance program and a trainer for daily physical activity stimulation. They also have access to teleconsultations with cardiologists and diabetes specialists as needed, telemonitoring of vital signs, and daily step tracking. An app records and monitors daily drug treatment, glycemia, blood pressure, heart rate, and other clinical parameters. Patients can also self-report symptoms and communicate via a chat and videoconference system with a Nurse Case Manager. The control group receives routine care. Data collection occurs before intervention and 6 months after baseline during a new outpatient cardiology evaluation. The primary outcome is to measure the difference in the distance walked during a 6-min walk test between baseline and after 6 months. The key secondary outcomes include improving the disease status and physical activity profile. Data will be analyzed according to the intention-to-treat principles.

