#### Outcome assessments

##### Primary outcome measures

The primary outcome is exercise tolerance improvement measured by the difference in the meters walked at the 6MWT. The test measures the distance walked when subjects are asked to walk as fast as possible for 6 min, and performance in this test has been used to measure cardiovascular exercise capacity, particularly in patients with congestive heart failure [30] and diabetic patients [31].

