#### Sample size

Based on the literature analyzed [40, 41] of the experience developed over the years in patients with heart failure [42] and patients with a complex phenotype, SCC and COPD [19], followed by remote surveillance, we estimated a sample of 240 patients who could be evaluated to demonstrate efficacy on the primary outcome. The number should be sufficient to establish an anticipated difference of 45–50 m in walking distance at the 6MWT (primary endpoint) between the intervention and control group to demonstrate a statistically significant difference between groups applying a *t*-test with alpha = 0.80 and beta = 0.05. A mean of 360 m (SD = 115) was considered. We performed a comparison test between two independent means (unpaired data) with equal sd (sd1 = sd2 = sd) in the two groups. Therefore, assuming an SD = 115 and delta = 28,217, the sample is 208 patients, 104 per group. Thus, considering the 15% of patients not present at T6 for calculating the endpoint (dropout), the sample becomes 239.

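### The repeated-measures ANOVA with Bonferroni follow-up tests makes no single between-arm contrast decisive for the 6MWT and differs from the unpaired t-test used to size the trial

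*Protocol article*

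**What the plan says.** The abstract (Methods and analysis) defines the endpoint as a change over time: "The primary outcome is to measure the difference in the distance walked during a 6-min walk test between baseline and after 6 months". The Primary outcome measures section says "The primary outcome is exercise tolerance improvement measured by the difference in the meters walked at the 6MWT". Neither sentence states a contrast between arms.

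The Sample size section does state one. It anticipates "an anticipated difference of 45–50 m in walking distance at the 6MWT (primary endpoint) between the intervention and control group" and describes the calculation thus: "We performed a comparison test between two independent means (unpaired data) with equal sd". The SD is 115 m and the result is 104 evaluable patients per group.

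The Statistical analysis section gives one method for the treatment effect: "Two-way analysis of variance (ANOVA) will analyze the effects of the intervention for repeated measures (time and group"). It continues "A post hoc analysis will be conducted when the ANOVA" F ratio is significant; the follow-up is Student t-tests across both times and arms, with Bonferroni correction. It does not mention the group-by-time interaction, say which F ratio triggers the follow-up tests, or give the number of comparisons. No T0–T6 correlation or SD of change appears in the article.

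**The concern.** A time-by-group ANOVA produces three F ratios, and they answer different questions. The time F asks whether distance changed on average over both arms. The group F compares arms on the mean of T0 and T6, so a treatment effect present only at T6 is halved. Only the group-by-time F compares the change between randomised arms. The plan lets an unspecified F open a set of t-tests that includes within-arm changes, which are not randomised comparisons.

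Two things are at stake. First, a gain common to both arms is plausible: controls also receive leaflets and encouragement to be active (Control group section), and everyone repeats the walk test. Such a gain could be reported as a significant improvement in the intervention arm, and the endpoint wording does not prevent that. Second, the 80% power belongs to one unpaired t-test at 0.05. Whether the planned analysis keeps it depends on a choice the article leaves open.

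**Working it through.** **Inputs from the article:** difference 45 m (lower end of 45–50 m), SD 115 m, 104 per arm, significance level 0.05. **Assumed:** two-sided testing, T0–T6 correlation r from 0.3 to 0.8, equal SDs at T0 and T6, a shared gain of 15 m, and 2, 4 or 6 Bonferroni comparisons.

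**1. Reproducing the planned size.** The article prints "alpha = 0.80 and beta = 0.05". The figures work only with the labels exchanged, as alpha 0.05 and power 0.80. The standard error of a between-arm difference is 115 × √(2/104) = 15.95 m, so the noncentrality is 45/15.95 = 2.82. The noncentral t with 206 degrees of freedom gives 80.2% power, and 104 per arm is the smallest number reaching 80%. The stated 208 is therefore reproduced for one two-sided unpaired t-test.

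**2. Shared gain of 15 m, no treatment effect.** The SD of change is 115 × √(2(1 − r)). The time F pools 208 patients, so its standard error is SD/√208. The within-arm paired test has standard error SD/√104 and is judged at 0.05/4 = 0.0125.

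| r | SD of change | Time F: 15/SE | Significant | Within-arm: 15/SE | Significant |
|---|---|---|---|---|---|
| 0.5 | 115.0 | 15/7.97 = 1.88 | about 47% | 15/11.28 = 1.33 | about 12% |
| 0.7 | 89.1 | 15/6.18 = 2.43 | about 68% | 15/8.73 = 1.72 | about 21% |
| 0.8 | 72.7 | 15/5.04 = 2.97 | about 84% | 15/7.13 = 2.10 | about 33% |

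The between-arm tests stay under control. In simulations with a shared gain of 20 m (10,000 trials per setting), the interaction F was significant in about 5% of trials and the T6 between-arm t-test at 0.0125 in about 1.1%. With no effect of any kind, at least one of the three F ratios was significant in 14% of trials, which agrees with 1 − 0.95³ = 14.3%.

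**3. Power for a true 45 m effect, by deciding test.**

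- T6 t-test after Bonferroni: 71% (0.05/2), 62% (0.05/4), 56% (0.05/6).
- Group main effect: difference 45/2 = 22.5 m, SD 115 × √((1 + r)/2); 37%, 33%, 32% at r = 0.5, 0.7, 0.8.
- Interaction F: with two time points this is the between-arm t-test on change, SD 115 × √(2(1 − r)).
- Baseline-adjusted ANCOVA: residual SD 115 × √(1 − r²).

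| r | Interaction F | ANCOVA |
|---|---|---|
| 0.3 | 66% | 84% |
| 0.5 | 80% | 90% |
| 0.7 | 95% | 98% |

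The variance ratio of ANCOVA to change score is (1 − r²)/(2(1 − r)) = (1 + r)/2. This is below 1 for every r below 1, so ANCOVA is the more precise of the two throughout.

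**The case against.** A reader might infer that the trial can be declared positive on a time effect alone and that the calculated power is lost. The document supports neither statement without conditions.

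The Statistical analysis section introduces the ANOVA as the analysis of the intervention, and the Sample size section speaks of a difference between groups. The natural reading is therefore the interaction F. That is a valid randomised comparison of the change named in the abstract. It holds its 5% error under a shared gain, and its power is 80% at r = 0.5, rising to 99% at r = 0.8. The lower figures require the Bonferroni T6 test or the group main effect to be decisive, which the text allows but does not say. The t-tests are called post hoc, and the number of comparisons is assumed. Choosing a change or interaction test over ANCOVA is less efficient but not an error. A statistical analysis plan, not shown, may name the interaction.

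Most of this stands and limits the point. It does not remove it. The article sets out an F-ratio gate and t-tests across times as well as arms without giving any between-arm term priority, and this differs from the test that was powered. Even the interaction reading falls to 66% power at r = 0.3, and the article gives no correlation to exclude that.

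**Conclusion.** The point holds as a should-fix. The stated decision path leaves the decisive test open and does not match the test used for sizing. The risk of a misleading result lies in a main effect or a within-arm change being reported as evidence of benefit; the between-arm interaction test itself is sound. For a 45 m effect, power ranges from about a third (group main effect) to 95% (interaction at r = 0.7), depending on the choice. The false-signal rates rest on an assumed 15 m shared gain and on the correlation: they are much lower at r = 0.5 than at 0.8, so the upper figures should not be quoted alone. All power figures take SD 115 m and 104 evaluable patients per arm from the article.

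**What to change.** Name one primary test: ANCOVA of 6MWT distance at T6 on randomised group, adjusted for baseline 6MWT and for centre (each of the three centres has its own randomisation list), two-sided alpha 0.05. Report the adjusted difference in metres with its 95% confidence interval. For the primary outcome, remove the F-ratio gate and the Bonferroni t-tests, and present within-arm changes descriptively only. Word the primary outcome as a between-arm comparison in both the abstract and the Primary outcome measures section.

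The cost is wording. The 6MWT is already measured at T0 and T6 in all randomised patients, and no further patients are needed, since ANCOVA exceeds 80% power with 104 per arm at each correlation examined. The Trial status section describes recruitment as ongoing at submission and no interim analysis is planned, so on the article's account the test can be fixed before the arms are compared.

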### Trial structure

At time T0, for patients randomized in the study, the following information is collected:Demographic variables: age and genderClinical variables: ejection fraction, NYHA class, and comorbiditiesThe Cumulative Illness Rating Scale (CIRS) [29] measures the patient’s health status. Each item is evaluated according to an ordinal scale with increasing levels of severity: from 1 (absent pathology) to 5 (very severe pathology). Two measures are obtained:Severity Index (SI): the average of the scores of the first 13 categories (the maximum obtainable score is 5)Comorbidity Index (CI): the category numbers with equal or higher scores.

At times T0 and T6, in all patients randomized, the following information is collected:Physical variables: body mass index (BMI), abdominal circumferenceBiochemical parameters: glycated hemoglobin (HbA1c) and the amino-terminal fragment of Brain Natriuretic Peptide (NT pro-BNP).Evaluation of exercise capacity by the 6-min walk test (6MWT) [30, 31].The Physical Activity Scale for the Elderly (PASE) [32] assesses physical activity performed during the previous period.Quality of life is measured in the following ways:The Minnesota Living Heart Failure Questionnaire (MLHFQ) [33]. MLHFQ comprises 21 topics that evaluate how, over the past month, the various physical and emotional symptoms of HF have prevented you from living as you would like.The Diabetes Quality of Life (DQOL) questionnaire [34]. DQOL comprises 46 questions that investigate four areas: general satisfaction, the global impact of the disease, concerns about social relationships, and concerns about diabetic disease. The scores on each scale range from 0 to 100; higher scores correspond to a better quality of life.The validated Italian version of the 12-item Short Form Survey (SF-12) questionnaire [35, 36]. The SF12 has a 6-item Physical Component Summary (PCS) and a 6-item Mental Component Summary (MCS).

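### No transformation or alternative to ANOVA and t-tests is named for the effect on NT-proBNP; if the marker is skewed and left untransformed, power can fall well below the log-scale level

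*Protocol article*

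**What the plan says.** All references are to the Protocol article.

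- **Outcome.** The section Secondary outcomes measures defines disease status by NT-proBNP and HbA1c. The abstract ranks it: "The key secondary outcomes include improving the disease status and physical activity profile". Under Trial structure, both markers fall in the list headed "At times T0 and T6, in all patients randomized, the following information is collected".
- **Effect analysis** (Statistical analysis): "Two-way analysis of variance (ANOVA) will analyze the effects of the intervention for repeated measures (time and group". The next step is also parametric: "A post hoc analysis will be conducted when the ANOVA *F* ratio is significant for the Student *t*-test among times and groups", with Bonferroni correction. No outcome, scale or transformation is named.
- **Normality** (same section): "The Kolmogorov–Smirnov test will test the distribution and normality of variables". Two uses follow. One is descriptive: "median ± interquartile (IQ) range for variables without a normal distribution". The other is the baseline comparison: "To compare groups at T0, the Student *t*-test, the Mann–Whitney-Wilcoxon test for continuous variables".
- **Level** (same section): "Statistical significance is defined as *P* = 0.05". Sidedness is not given.

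**The concern.** The section expects some variables to be non-normal and has tools for them. It applies those tools to the summary tables and to the T0 comparison, where randomization already makes the arms comparable. For the effect of the intervention it names only methods based on means. A skewed marker would be summarised by its median, could be rank-tested at baseline, and would then be judged on arithmetic means for the trial's conclusion.

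For a marker that is right-skewed and changes in proportion to its level, this matters. As an illustration with invented values, a 20% fall from 8,000 is 1,600 units and a 20% fall from 400 is 80 units, so the first patient counts 20 times as much. The variance of change comes mainly from the same few patients. At stake are the power for one of the two disease-status markers and whether the estimate describes the typical patient. The t-tests are conditional on a significant F ratio, so a missed F test also removes the follow-up comparison.

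**Working it through.** **1. The plan's own figures.** The plan gives no SD, distribution or expected effect for NT-proBNP. Only the number of patients carries over. The stated 104 per group reproduces for the walk test: a difference of 45 m, SD 115 m, two-sided 0.05 and power 0.80 give 103.5, rounded up to 104. If 239 are randomized and 15% have no T6 value, 239 × 0.85 = 203 remain, about 102 per arm. The table uses 104.

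**2. Assumptions from outside the documents.** NT-proBNP is log-normal at T0 and T6, with log-SD s of 0.8, 1.0 or 1.2 and log-scale correlation ρ of 0.7, 0.8 or 0.9. The intervention multiplies T6 by 0.75. Tests are two-sided at 0.05. The intervention effect is read as the group-by-time interaction. With two time points, its F statistic is the square of the t statistic comparing change between arms.

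**3. Central case by formula (s = 1.0, ρ = 0.8, n = 104 per arm).**

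- *Log change.* Effect = −ln 0.75 = 0.2877. SD of change = s√(2(1−ρ)) = √0.4 = 0.6325. SE = 0.6325 × √(2/104) = 0.0877. Effect/SE = 3.28, so power ≈ Φ(3.28 − 1.96) = 0.91.
- *Log T6 adjusted for log T0.* Residual SD = s√(1−ρ²) = 0.6. SE = 0.6 × √(2/104) = 0.0832. Effect/SE = 3.46, so power ≈ Φ(1.50) = 0.93.
- *Untransformed change, in units of the T0 mean.* Effect = 0.25. Control variance = 2[(e^1.0 − 1) − (e^0.8 − 1)] = 2(1.7183 − 1.2255) = 0.9855. Intervention variance = 1.7183 × (1 + 0.75²) − 2 × 0.75 × 1.2255 = 0.8465. SE = √((0.9855 + 0.8465)/104) = 0.1327. Effect/SE = 1.88, so power ≈ Φ(−0.08) = 0.47. The normal approximation is rough here because of the skew; simulation gives 0.52.

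**4. Simulation (2,000 trials per setting, 104 per arm, 25% fall).**

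| log-SD | ρ | Untransformed change | Log change | Log, T0 covariate |
|---|---|---|---|---|
| 0.8 | 0.7 | 67% | 92% | 96% |
| 0.8 | 0.8 | 80% | 98% | 99% |
| 0.8 | 0.9 | 96% | 100% | 100% |
| 1.0 | 0.7 | 40% | 76% | 82% |
| 1.0 | 0.8 | 52% | 91% | 93% |
| 1.0 | 0.9 | 78% | 99% | 100% |
| 1.2 | 0.7 | 25% | 62% | 69% |
| 1.2 | 0.8 | 31% | 77% | 82% |
| 1.2 | 0.9 | 51% | 97% | 98% |

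At 102 per arm the ranges are about 23–96%, 60–100% and 66–100%. Over falls of 20% to 30%, untransformed power runs from 17% to 99%, and it is below log-scale power in every setting with a true fall.

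**5. Dominance.** The 10 largest of 208 squared deviations of untransformed change (4.8% of patients) carry 57% (s = 0.8) to 77% (s = 1.2) of the within-group sum of squares.

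**6. No effect.** Rejection rates are 3.6–5.1% untransformed and 3.7–6.6% for the two log-scale tests. The log-scale tests are exact under these assumptions, so their spread is simulation error.

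**The case against.** The strongest reply is that the text never says NT-proBNP will be analysed as measured. Taking logs and then running the stated ANOVA would comply with every word. The source is a condensed article, and a full protocol exists and an analysis plan may. The scale of one biomarker is a detail that such documents often hold. A reader might infer that the plan has fixed a raw-scale analysis; the documents do not support that. What they show is narrower: within one section, alternatives for non-normal variables are named for two purposes and not for the effect analysis.

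Second, skew, spread, correlation and effect size all come from outside the documents. The simulated effect is uniformly proportional, which favours logs. Eligibility also selects ambulatory patients with no recent admission for decompensation, which may limit extreme values. This stands, and is why the result is conditional and given as a range.

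Third, a reader might infer that a real proportional fall would probably be missed. The range does not support this either: for a 25% fall, untransformed power is 67–96% at log-SD 0.8, and only at log-SD 1.2 with correlation 0.7 or 0.8 does it fall to about a third or less.

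Fourth, validity is not threatened, and the choice between arithmetic and geometric means is partly a choice of estimand. That is true. Baseline adjustment is also a separate gain, of 0 to 7 percentage points in the table; most of the recovery comes from the log scale.

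**Conclusion.** The point holds as an avoidable weakness in the analysis of one key secondary marker. The normality check has no stated consequence for the effect analysis, and the only methods named for that analysis compare means. If NT-proBNP is right-skewed and left untransformed, the estimate is dominated by a few patients. Under the stated assumptions for a 25% fall and about 102 per arm, power is about 23–96%, against 60–100% on log change and 66–100% on the log scale with baseline adjustment. In the central case the loss is roughly 40 percentage points (52% against 91–93%).

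The harm is lost power and an estimate that represents the typical patient poorly, not false positives. The walk-test outcome and its sample size are untouched. If the sponsor does intend a transformation, writing it down still matters: otherwise the scale could be chosen after the outcome data have been seen.

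**What to change.** Add to Statistical analysis: NT-proBNP is log-transformed; log(T6) is compared between arms with log(T0) as covariate; the effect is reported as the ratio of geometric means, intervention to control, with its 95% CI. HbA1c can stay on its own scale, and untransformed NT-proBNP can be summarised by median and interquartile range, as the section already allows for non-normal variables. Set this before outcome data are examined by arm. If the full protocol or an analysis plan already says it, a cross-reference is enough.

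The cost is about one sentence, with no new data or patients. The small downside is that the effect is read as a ratio instead of a difference in concentration.

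### The on-treatment analysis, as defined, cannot show whether protocol deviations caused bias, and it gives no check on dropout

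*Protocol article*

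**What the plan says.** All of this is in the protocol article.

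- **Primary population** (Statistical analysis): "Data will be primarily analyzed according to the intention-to-treat principle". Treatment effects are examined with a two-way repeated-measures ANOVA with factors time and group.
- **Supporting analysis** (same section): "An on-treatment analysis will be subsequently performed to assess whether protocol deviations have caused bias". Participants with a documented deviation are removed, and these are exemplified as "patients in the intervention group who received only some of the intervention or participants in both groups with incomplete follow-up data". Partial receipt is thus a ground for exclusion in the intervention group only, while incomplete follow-up is one in both groups. No amount of the programme is named below which a patient counts as a partial receiver.
- **Time points** (Abstract, Methods and analysis): "Data collection occurs before intervention and 6 months after baseline during a new outpatient cardiology evaluation". There are two, T0 and T6.
- **Expected loss** (Sample size): "considering the 15% of patients not present at T6 for calculating the endpoint (dropout), the sample becomes 239".
- **Control care** (Control group): standard care, advice and leaflets, with no programme to follow.

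The article does not say how a missing T6 walk enters the intention-to-treat analysis.

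**The concern.** An analysis meant to detect bias should not bring in a new bias of unknown size. Here the intervention arm is filtered on behaviour after randomisation and the control arm is not filtered in the same way. If patients who keep up with calls, tracker and app would have changed differently in walking distance anyway, the on-treatment difference moves even when the programme does nothing. A reader who sees the two results differ cannot tell whether deviations diluted a real effect or the selection created one. A reader who sees them agree may be reassured without good reason.

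The second part concerns dropout. The on-treatment set removes patients with incomplete follow-up. If the primary ANOVA also gains nothing from them, the two analyses share the same gap, and their agreement says nothing about whether missing T6 walks distorted the comparison. In heart failure a missed 6-month walk may well be related to deterioration.

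**Working it through.** **1. The plan's own figures.** With a difference of 45 m (the lower end of "an anticipated difference of 45–50 m in walking distance at the 6MWT (primary endpoint) between the intervention and control group"), SD 115 m, two-sided alpha 0.05 and power 0.80, a noncentral-t calculation gives 104 per group, or 208, as the article states. Then 208 × 1.15 = 239.2, which matches 239. The printed delta and the alpha and beta labels do not give 208. That is a separate matter and does not bear on this point. Of 239 patients, 15% is about 36 without T6, leaving about 203.

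**2. What the ANOVA does with a patient who has T0 only.** With two times and a subject effect, a patient with one observation is fitted exactly and leaves nothing for the group-by-time term. A check on simulated data (40 patients, 5 without T6) gave a group-by-time F of 1.6815. The squared two-sample t on change scores in completers was also 1.6815. Without imputation, the treatment contrast is therefore the completers' contrast.

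**3. Size of the on-treatment shift when the true effect is zero.** The documents give no adherence figures, so everything in this step is assumed.

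*First parametrisation.* Take a T0–T6 correlation of 0.7. The SD of change is 115 × √(2 × (1 − 0.7)) = 89 m. If the least adherent fraction q of the intervention arm is removed and adherence correlates r with change, the shift is r × 89 × φ(z_q)/(1 − q).

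| r | q = 20% | q = 30% | q = 40% |
|---|---|---|---|
| 0 | 0 m | 0 m | 0 m |
| 0.1 | 3.1 m | 4.4 m | 5.7 m |
| 0.2 | 6.2 m | 8.8 m | 11.5 m |
| 0.3 | 9.3 m | 13.3 m | 17.2 m |
| 0.4 | 12.5 m | 17.7 m | 22.9 m |

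At q = 30% and r = 0.3, with 104 × 0.7 = 72.8 adherers against 104 controls, SE = 89 × √(1/72.8 + 1/104) = 13.6 m. The chance of a significant result is then about 16% instead of 5%. The 13.3 m shift is 13.3/45 = 30% of the target.

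*Second parametrisation.* If a share f of the arm is excluded and adherers exceed non-adherers by g metres, the shift is f × g. For f = 10–30% and g = 20–60 m this is 2 to 18 m (4% to 40% of 45 m). With SD 115 m and 102 per arm before exclusion, the false-positive rate runs from about 5% to 17%.

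**4. Size of dropout bias in a completers' analysis.** If patients lost would have walked g metres less than completers in both arms, the bias is (loss in intervention − loss in control) × g.

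- 15% versus 15%: 0 m for any g.
- 20% versus 10%, g = 60 m: 0.10 × 60 = 6 m (2 m at g = 20 m).
- 25% versus 5%, g = 20–60 m: 4 to 12 m.

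The loss split and g are also assumptions. The article gives only the overall 15%.

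**The case against.** The strongest reply is that intention-to-treat is declared primary and the on-treatment analysis comes after it, so the main conclusion does not rest on the flawed set. That stands, and it limits the weight of the point.

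The one-sided adherence exclusion also follows from the design, because controls have no programme to adhere to. This explains the asymmetry but does not remove the selection. It is the reason why exclusion is a poor tool for the stated question.

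Three stronger readings are tempting, and the documents do not support them.

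- *The intention-to-treat analysis is restricted to patients with a T6 value.* No section says so. The 15% is a sample-size allowance, not a rule for an analysis set, and an analysis plan that is not shown could impute. The statement holds only if nothing is imputed.
- *Most intervention patients would be excluded.* Exclusion needs a documented deviation, and nothing makes a missed call or an unworn tracker one. The missing threshold leaves the share unknown, and unknown does not mean large.
- *The on-treatment result will favour the intervention.* That assumes adherers do better. With no relation between adherence and change the shift is zero, and if stable patients disengage because they feel well it could go the other way.

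It is also fair to say that the analysis is aimed at bias from protocol deviations, not at dropout as such. Dropout enters because incomplete follow-up is listed among the deviations.

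**Conclusion.** The first part is firm because it rests on what the article states. The rule selects on post-randomisation behaviour in one arm, without a threshold, and removes incomplete follow-up in the same step. Its difference from the intention-to-treat result cannot be attributed to bias from deviations.

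The second part is conditional. If T6 values are not imputed, the primary ANOVA takes no information on the group-by-time effect from the expected 15%, and comparing the two analyses cannot reveal dropout bias. If they are imputed, that part falls away for the primary analysis, but the on-treatment set still provides no check on dropout.

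The sizes illustrate what could happen and are not predictions. The on-treatment shift runs from 0 m to roughly 20 m (18 m and 23 m at the far ends of the two parametrisations). Dropout bias is 0 m with equal loss and the same deficit in both arms, and 6 m at 20% versus 10% loss with a 60 m deficit. The upper values are material against 45 m and the lower ones are not. The change is worth making, but the flaw does not undermine the choice of intention-to-treat as primary.

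**What to change.** 1. State that all randomised patients are analysed as allocated. Use a likelihood-based, baseline-adjusted mixed model in which T0 and T6 are both outcomes, so that patients with T0 only stay in, or use multiple imputation of T6. Add a sensitivity analysis for data missing not at random.
2. Call the on-treatment analysis descriptive, define partial receipt of the intervention before the analysts are unmasked, and delete the statement that it assesses whether deviations caused bias.
3. Optionally, add a complier-average causal effect estimate with randomisation as the instrument, but only if its exclusion restriction can be defended. Patients below any adherence cut-off still receive part of the programme and may benefit, in which case the estimate would overstate the effect in compliers.

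The cost is wording in the analysis section and modest programming, with no new data collection. A complier-average estimate, if added, would have a wider interval than the on-treatment one.
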